### Data collection and management

Primary and secondary outcomes are collected with six prospective primary data sources and one secondary data source.

Data source 1 [DS1] is the project database based on REDcap to document patient cases, events and process data, e.g., sociodemographic data, outpatient appointments, and clinical outcomes at baseline and 6, 12, 18 and 24 months after cellular therapy. Baseline clinical status is defined as the patient’s clinical status on the day of discharge from the index hospitalization. Data quality is monitored through automated verification of the recorded data, notifications regarding missing entries, and regular monitoring at the three study centers.

Data source 2 [DS2] are validated QoL surveys. To evaluate the QoL of patients after alloHCT or CAR T-cell therapy, the survey instruments EORTC QLG Core Questionnaire (EORTC QLQ-30) and the module for low-grade non-Hodgkin lymphoma (EORTC QLQ-NHL-LG20) [17] as well as the German version of the NCCN Distress Thermometer [18] are used. QoL data is evaluated at baseline and 6, 12, 18 and 24 months after discharge (Table 1).

Data source 3 [DS3] is an online-survey to evaluate satisfaction of patients with the SPIZ program. We use an adjusted version of the validated survey instrument Patient Satisfaction with Cancer Care (PSCC) [19] to evaluate satisfaction with the follow-up care in general for both intervention and control group. Additionally, we developed specific questions for each SPIZ component to measure satisfaction within the intervention group. These questionnaires are sent to patients via e-mail as an online survey 12 months after discharge and at the end of the study.

Data source 4 [DS4] is the SMILe App. Patients in the intervention group are provided with the SMILe App for their mobile phones and continuously document their health status, including vital parameters and symptoms (e.g., body temperature, body weight), and well-being. With the SMILe App, data is stored over time.

With data source 5 [DS5] and data source 6 [DS6] qualitative empirical data is collected. [DS5] comprises semi-structured individual telephone interviews with patients and health care providers. We conduct twenty-four qualitative interviews with patients from the three participating cell therapy centers (four interviewees from the intervention group and four interviewees from the control group from each center, respectively) about their experiences and satisfaction with their post-treatment care approximately six months after discharge. In order to reflect the heterogeneity of the patient group, the selection occurs based on purposeful sampling i.e. with respect to age, gender, type of therapy, distance between place of residence and hospital, level of education and occupational status. In addition, we conduct twelve interviews with healthcare providers across all three participating study sites. That is to say, at each site, one hematologist from the cell therapy center, one community-based hematologist, one onco nurse and one case manager will be interviewed to integrate the perspectives of all in post-treatment care involved healthcare providers. All interviews will be audio recorded and transcribed verbatim with the help of the speech recognition software AlphaSpeech (Version 1.9.0, hosted on servers of TUD Dresden University of Technology), followed by manual corrections. A focus group interview with healthcare providers of the three cell therapy centers will be [DS6]. The focus group interview will be audio recorded and transcribed as described for the qualitative interviews above.

Routine data from the participating statutory health insurance provider, AOK PLUS, will be used as data source 7 for all patients insured with this provider [DS7.

Fidelity measures include successful app onboarding, the frequency of app entries and data reviews, the number and type of case management contacts, home visits and video consultations, participation in case conferences, completion of scheduled assessments, and deviations from the planned intervention pathway. As the intensity of several components is tailored to participants’ clinical needs, no minimum number of home visits, video consultations, or case conferences is required. Intervention delivery is considered to have commenced once the participant has completed SPIZ onboarding, is discharged from index hospitalization, and has used at least one component of the SPIZ intervention. To minimize contamination, the SPIZ-specific components are organized separately and provided only to participants allocated to the intervention group. Control-group participants are not enrolled into the SMILe App, assigned to a SPIZ case manager, proactively monitored by the onco nurses, or included in protocol-specific home visits, video consultations, or case conferences. Clinically necessary care will never be withheld from either group. All potential primary endpoint events will be adjudicated by two board-certified hematologists who are blinded to treatment allocation. Any disagreements will be resolved by consensus or, if necessary, by a third board-certified hematologist who is also blinded to treatment allocation.

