**Fig. 2 Fig2:**
[figure not shown]
Patient pathway in the SPIZ RCT: After enrollment, patients are randomized in a 1:1 ratio to either the SPIZ group or the control group. In the SPIZ group, home visits by onco nurses are carried out as needed and alternate with routine outpatient clinic visits. Patients document vital signs and symptoms daily via the SMILe App, which are monitored by onco nurses. Regular video consultations with hematologists at the cell therapy center take place, either following home visits or on demand. Patients in the control group receive routine post-treatment care. Onco nurse: oncology nurse; R: randomization

Home visits by an onco nurse are scheduled at predefined time points (supplementary Figs. 1 and 2) and constitute a planned component of the intervention. Together with a subsequent video consultation, each scheduled home visit replaces a routine outpatient visit at the center. Additional home visits may be arranged when clinically indicated. Multidisciplinary case conferences are scheduled at week 6, week 12, month 6, month 12 and month 24 (supplementary Figs. 1 and 2).

Home visits by an onco nurse combined with video consultations replace some visits to the cell therapy center in comparison with standard of care. Besides that, participants in the intervention group continue to receive all routinely indicated outpatient visits, diagnostic assessments, treatments, and access to emergency care at their treating center. Additional home visits, video consultations, app-supported monitoring, case management, and multidisciplinary case conferences are supplementary components. Participants in the control group receive usual standard of care without the protocol-specific SPIZ components.

Missed app entries, unsuccessful attempts to contact a participant, and the outcome of each contact attempt are documented in the hospital information system and, separately, in the REDCap database. When app entries are missing, the case manager or onco nurse make repeated attempts to contact the participant. If the participant remains unreachable, the responsible physician is informed, and further action is taken in accordance with the respective center’s standard operating procedures.

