### Sample size

Sample size calculation for the primary study population is based on the primary endpoint. The literature available at the time of sample size planning showed that there was a rehospitalisation rate of 55% after alloHCT in a German population [10]. Given that deceased patients were typically hospitalised beforehand, it can be inferred that the 55% figure accurately represents the routine clinical care. The SPIZ program should reduce the mortality or disease-specific rehospitalisation rate to 35% or less. The case number calculation was performed with a one-sided Fisher test. Given a significance level of 5% and a yielded power of 80%, it is assumed that 143 patients in the intervention group and 143 patients in the control group are required (calculated with GPower 3.1). With an estimated drop-out rate of 5%, 302 patients must be included.

While disease- and cell therapy-specific rehospitalization or death includes all complications typically associated with the underlying hematological condition or cell therapy, other reasons for rehospitalization or death are defined as independent, e.g., joint replacement due to arthrosis, or an accident. The analysis of the primary endpoint will be conducted one year after primary hospital discharge of the last enrolled patient. Death or rehospitalization are considered equivalent primary endpoints.

Recruitment of health care providers involved in SPIZ (secondary study population) for twelve qualitative interviews starts 18 months after initiation of patient enrollment.

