### Data analysis of secondary hypothesis d)

The health economic evaluation of the SPIZ program focuses on a comparison between the intervention and control groups in terms of inpatient stays and the resulting costs for the statutory health insurance AOK PLUS. The latter is the statutory health insurance fund with the most insured persons in the catchment area, thus ensuring a sufficient number of test subjects for analysis.

These are standardized over the entire observation period in terms of number of stays, average length of inpatient stays, and costs per observation year.

Further analyses relate to the comparison between the two groups in terms of selected outpatient costs, costs for medications dispensed in pharmacies, patient travel costs, care level, and number of patients in palliative care.

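### Readmissions counted in the primary endpoint may be detected differently in the two arms, and no match to the arm-neutral AOK PLUS inpatient records is described

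*Protocol article*

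**What the plan says.** All references are to the protocol article.

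- **Endpoint.** Hypotheses and outcomes defines the primary endpoint as death or unplanned readmission for complications of the hematologic disease or the cell therapy, tested at 12 months. Patients may live up to 200 km from a centre (Eligibility criteria).
- **Sources for clinical events.** Data collection and management says that seven sources together serve the primary and secondary outcomes. It ties none of them to the primary endpoint. REDCap records cases, events and process data, including "clinical outcomes at baseline and 6, 12, 18 and 24 months after cellular therapy". Table 1, hypothesis a), names REDCap and the SMILe system for a block of outcomes that includes mortality and unplanned readmissions.
- **Contact in the SPIZ arm.** Patients make daily app entries that nurses review. When entries are missing, "the case manager or onco nurse make repeated attempts to contact the participant" (Enrollment, randomization and patient pathway).
- **Contact in the control arm.** There is no app, case manager or proactive nurse monitoring (Data collection and management).
- **Adjudication.** Two hematologists blinded to allocation review all potential primary events.
- **Insurer data.** "Routine data from the participating statutory health insurance provider, AOK PLUS, will be used as data source 7 for all patients insured with this provider". Table 1 lists this source only under hypothesis d), for rates and costs of readmission among other items. The analysis section for hypothesis d) describes a "comparison between the intervention and control groups in terms of inpatient stays and the resulting costs for the statutory health insurance AOK PLUS", with number and length of stays as well as costs.

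**The concern.** A readmission to a local hospital counts only if the trial team learns of it. The SPIZ arm has extra channels through which the team can learn of it, and one of the two sources named in Table 1 does not exist for controls. Adjudicators see only what has been found, so blinding them cannot restore an admission that nobody reported.

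If the arms differ in the share of events found, the observed difference mixes the effect of the programme with the effect of looking harder in one arm. Fewer events found among controls would hide a real benefit. Fewer found in the SPIZ arm would create an apparent one. AOK PLUS records inpatient stays without regard to allocation, and the trial already obtains these data. No step is described that uses them to check whether primary events were captured equally.

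**Working it through.** **Inputs.** From Sample size: "The case number calculation was performed with a one-sided Fisher test", level 5%, 80% power. For the control rate, "there was a rehospitalisation rate of 55% after alloHCT in a German population". The programme should "reduce the mortality or disease-specific rehospitalisation rate to 35% or less". From Results: 153 patients per arm. The analysis section names Fisher's exact test without giving a side, so the planning side is assumed here. The documents give no capture rates. The missed shares below are assumptions.

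**Formula.** Power = Σ over x, y of Bin(x; n, p_C) × Bin(y; n, p_S) × 1[p_Fisher(x, y) ≤ 0.05]. Here p_Fisher is the one-sided hypergeometric tail for few SPIZ events. If a share m of event patients in an arm is missed, that arm's rate p becomes p(1 − m).

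**The plan's own figure.** At 55% versus 35%, this calculation needs 85 per arm for 80% power. The stated 143 per arm gives 95.6%. The dropout step does reproduce: 286 / 0.95 = 301.05, rounded up to 302. The 143 is a separate matter; here it means only that the trial has spare power if 35% is reached. At 153 per arm and full capture, power is 96.1%, and the chance of a false benefit with 55% in both arms is 3.7%.

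**Scenario A: control events missed, SPIZ events all found, true rates 55% and 35%.**

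| Missed share of control event patients | Observed control rate | Observed difference (points) | Power |
|---|---|---|---|
| 0% | 55.0% | 20.0 | 96% |
| 5% | 0.55 × 0.95 = 52.3% | 17.3 | 90% |
| 10% | 0.55 × 0.90 = 49.5% | 14.5 | 79% |
| 15% | 0.55 × 0.85 = 46.8% | 11.8 | 62% |

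With 153 × 0.55 ≈ 84 control event patients expected, these shares are about 4, 8 and 13 patients.

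**Scenario B: SPIZ events missed, control events all found, no true effect (55% in both arms).**

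| Missed share of SPIZ event patients | Observed SPIZ rate | False-benefit rate |
|---|---|---|
| 0% | 55.0% | 3.7% |
| 5% | 52.3% | 10% |
| 10% | 49.5% | 21% |
| 15% | 46.8% | 37% |

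**What the model leaves out.** The loss is applied to the whole composite. The endpoint is binary, so a patient is misclassified only if every qualifying event by month 12 is missed, death included. Full capture of deaths would therefore make both effects smaller.

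**The case against.** The strongest reply is that the article condenses a fuller protocol. How outside admissions are found (discharge letters, patient queries, source checks) is commonly left to that document, so its absence here proves nothing. This stands: the point is not that a procedure is missing. What the article does state is the unequal contact, the named sources and the place given to insurer data.

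Four stronger readings are tempting, and the article does not support them.

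- *Insurer data serve only for costs.* Table 1 and the analysis of hypothesis d) also use rates, number and length of stays. An arm comparison of stays in AOK PLUS patients is therefore already planned. It covers the whole observation period and is not described as limited to unplanned, disease-related stays, so it does not show which primary events were missed.
- *Readmissions are captured only every six months.* The schedule is attached to clinical outcomes in a list of examples. REDCap also documents events, the planned survival analyses of hospitalisation need dates, and there are missing-entry notices and site monitoring. Those checks still cannot reveal an admission that was never reported.
- *Controls are under-observed, so the bias runs against SPIZ.* Each scheduled home visit with its video consultation replaces a centre visit that controls keep, and contact declines after about day 100 in both arms. The Table 1 source entry also covers symptom burden, so the SMILe system may be meant mainly for that. Neither direction is established.
- *The loss of power is severe.* With a SPIZ rate of 40%, power would fall from 81% to 65%, 46% or 28%. The document does not state 40%; it plans for 35% or less. At 35%, a 10% loss among controls still leaves 79%, close to the planned 80%.

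**Conclusion.** The point holds as a risk that the trial can measure, not as a demonstrated bias. Detection of readmissions may differ by arm, blinded adjudication does not address that, and no match of the arm-neutral inpatient records to primary events is described. The scenarios show that the result is sensitive in either direction: at a 10% one-sided loss, power is 79% instead of 96%, or the false-benefit rate is 21% instead of 3.7%. These figures rest on assumed missed shares, a one-sided 5% Fisher test, loss in one arm only and no separate treatment of deaths. An inflated type I error does not follow unless capture is lower in the SPIZ arm, which nothing in the article shows. This is a worthwhile, inexpensive improvement and does not call the design into question.

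**What to change.** Before database lock:

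1. Match AOK PLUS inpatient stays (dates and diagnoses) to REDCap readmissions for all AOK-insured patients in both arms.
2. Send every unmatched stay to the blinded adjudicators.
3. Report the capture rate by arm.
4. Add a sensitivity analysis of the 12-month composite in AOK-insured patients, using claims-identified admissions plus deaths.

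If the full protocol already sets out one event-finding procedure for both arms, cite it beside the endpoint definition.

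Test, sample size and primary analysis stay as they are. The cost is one linkage step on data already planned and one extra analysis; with first results expected in mid-2027, there is time. The check reaches only AOK-insured patients, whose share of the sample is not stated. It depends on when claims are delivered and may need a data-protection check. A uniform admission question at months 6 and 12 could not fill the gap for everyone: enrollment ran from January 2024 to January 2026, so many patients had passed those times by its close.

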### Data analysis regarding primary hypothesis and secondary hypothesis a)

The confirmatory test of the primary outcome at 12 months will be performed using Fisher’s exact test. All outcomes of secondary hypothesis a) are presented descriptively for the intervention and control groups according to the respective survey dates. The same applies to the primary combined outcome at time points 6, 18, and 24 months. Metric values will be compared between groups in terms of their means or, in the case of skewed distributions, their medians; categorical values will be compared in terms of their distributions. For events (death/ complication/ hospitalisation), survival time analyses and hazard ratios will be calculated. Logistic or Poisson regressions will be used to estimate effect size measures (odds ratios or relative risks). In addition, the control and intervention groups will be compared with regard to potential confounders. Should serious biases occur despite randomization, these will be addressed as appropriate through adjustments, subgroup analyses, or sensitivity analyses.

### Data analysis of secondary hypothesis b) and c)

We descriptively analyze quantitative survey data for assessing QoL [DS2] and satisfaction of patients with the SPIZ program [DS3] as described for the testing of secondary hypothesis a). For the intervention group, a comparison will also be made with the services provided for in the pathway.

To further evaluate patients’ satisfaction/dissatisfaction with SPIZ and its components, the transcripts of the 24 qualitative interviews with patients [DS5] will be qualitatively analysed using deductive and inductive coding [20] and analysed computer-assisted with MAXQDA 24 (VERBI Software 2023). In order to achieve intersubjective comprehensibility [21] two researchers conduct the coding process consecutively and independently. Any differing or unclear coding will subsequently be discussed and resolved jointly.

Satisfaction of health care providers with the SPIZ program will be assessed with a qualitative content analysis of the interview transcripts as described above. Based on the results of the qualitative interview analysis, we explore and discuss potential facilitators and barriers to the implementation of the SPIZ program into routine healthcare in a focus group with health care providers [DS6]. The focus group will be analysed as described above for qualitative individual interviews.

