### Hypotheses and outcomes

The primary hypothesis is that patients receiving the SPIZ intervention following cellular therapy (intervention group) experience better health outcomes in terms of lower mortality and fewer hospital readmissions than patients receiving routine clinical care (control group). The target population comprises all adult patients with hematologic diseases who undergo alloHCT or CAR T-cell therapy at one of the three participating centers.

Efficacy will be evaluated using a composite primary endpoint comprising mortality and disease-related rehospitalization. The latter is defined as unplanned rehospitalization due to complications typically associated with either the underlying hematologic disease (e.g., disease progression) or cellular therapy. Such complications include infections and organ toxicities following either therapy, GvHD following alloHCT, and CRS or neurotoxicity, such ICANS, following CAR T-cell therapy. The primary endpoint will be evaluated by confirmatory statistical analysis 12 months after cellular therapy.

Secondary hypotheses with corresponding outcomes and data sources are listed and described in Table 1.

**Table 1 Tab1:** Overview of the secondary hypotheses. The four secondary hypotheses to be examined are listed along with their corresponding secondary outcomes and the respective data sources or scales

Secondary hypotheses	Secondary outcomes	Data source / scale
a) SPIZ leads to improved longitudinal clinical outcomes	◼ Mortality ◼ Complications, e.g., infections, GvHD (alloHCT), CRS (CAR T-cell therapy), neurotoxicity (CAR T-cell therapy), relapse, and death assessed by incidence and duration (as feasible) ◼ Rates and duration of unplanned rehospitalizations ◼ Symptom burden, including nutrition, body weight, body temperature, skin changes, bowel habits, and neurological symptoms ◼ Laboratory values ◼ Therapy adjustments ◼ Conducted assessments, e.g. staging, pulmonary function testing, echocardiography	REDCap-based project database, SMILe system
b) SPIZ leads to improvements in QoL and patient empowerment	QoL assessed using established questionnaires	EORTC QLG Core Questionnaire QLQ-C30 and module for low-grade non-Hodgkin lymphoma QLQ-NHL-LG20 [17], NCCN Distress-Thermometer (German version) [18]

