### Principles of the analyses

All analyses within the scope of the SPIZ evaluation are carried out in the intention-to-treat population. Missing values are identified, and their underlying mechanisms are examined in terms of randomness. When values are missing, the individuals in question are excluded from the respective sub-analyses. The results of the evaluation are published in full, transparently, and independently of the outcome of the evaluation. The method chapter is based on the SPIRIT reporting guidelines [22]. Reporting is based on the CONSORT and TIDieR guidelines [23, 24].

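### Quality of life is compared only as group means or medians per visit among respondents; the baseline score is not used, which costs precision and makes hypothesis b) harder to interpret

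*Protocol article*

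**What the plan says.** Table 1 (*Hypotheses and outcomes*) states hypothesis b) as a directional claim: "SPIZ leads to improvements in QoL and patient empowerment". The QoL instruments are QLQ-C30, QLQ-NHL-LG20 and the Distress Thermometer. *Data collection and management* gives the schedule: "QoL data is evaluated at baseline and 6, 12, 18 and 24 months after discharge".

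The analysis is fixed in three places.

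- *Data analysis of secondary hypothesis b) and c)* calls it descriptive: "We descriptively analyze quantitative survey data for assessing QoL [DS2] and satisfaction of patients with the SPIZ program [DS3". It refers back for the method: "as described for the testing of secondary hypothesis a".
- *Data analysis regarding primary hypothesis and secondary hypothesis a)* gives that method: "All outcomes of secondary hypothesis a) are presented descriptively for the intervention and control groups according to the respective survey dates". It continues: "Metric values will be compared between groups in terms of their means or, in the case of skewed distributions, their medians". Adjustment, subgroup or sensitivity analyses follow only if serious biases arise despite randomization.
- *Principles of the analyses* sets the missing-data rule: "When values are missing, the individuals in question are excluded from the respective sub-analyses". The sentence before it says that the mechanisms of missingness will be examined, but no change of method is tied to the result.

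**The concern.** The trial collects a baseline QoL score and then names no use for it. The other methods listed for hypothesis a) do not fill the gap: survival analyses and hazard ratios are for events, and the logistic or Poisson regressions are there to give odds ratios or relative risks. A metric questionnaire score is left with a mean or a median per visit.

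Two things are at stake. The first is precision: a patient's baseline score usually predicts part of the later score, and an unadjusted comparison leaves that part in the error. The second is interpretation. The introduction describes patients at high risk of death and severe complications, and the intervention is meant to lower mortality. The patients who answer at 12 months may therefore differ between arms, and a per-visit mean does not account for it. In addition, a choice between mean and median that depends on skewness lets the effect measure change between scales and visits.

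The point concerns the QoL scales only. The satisfaction survey is sent at 12 months and at the end of the study, so it has no baseline to adjust for.

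**Working it through.** The article gives no planning figure for QoL (no SD, effect size, correlation or completion rate), so there is nothing to reproduce. The check asks what the unused baseline is worth.

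**Inputs.** 153 patients per arm (*Results*); 1:1 allocation (*Enrollment, randomization and patient pathway*). Assumptions: baseline to follow-up correlation r from 0.3 to 0.7; follow-up completion of 100% or 70% (0.7 × 153 ≈ 107 per arm); two-sided 5% and 80% power, used only as a yardstick for precision.

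**Precision.** In units of the score's SD:

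- unadjusted standard error = √(2/n); for n = 153, √(2/153) = 0.114
- detectable difference = (1.960 + 0.842) × √(2/n); for n = 153, 2.802 × 0.114 = 0.320; for n = 107, 0.383
- with baseline as covariate, the variance is multiplied by 1 − r², the interval width by √(1 − r²), and the effective number of patients by 1/(1 − r²)

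| r (assumed) | Variance factor | Interval width factor | Equivalent patients | Detectable difference, 153 per arm | Detectable difference, 107 per arm |
|---|---|---|---|---|---|
| unadjusted | 1 | 1 | 1 | 0.320 SD | 0.383 SD |
| 0.3 | 0.91 | 0.95 | 1.10 | 0.306 SD | 0.365 SD |
| 0.4 | 0.84 | 0.92 | 1.19 | 0.294 SD | 0.351 SD |
| 0.5 | 0.75 | 0.87 | 1.33 | 0.277 SD | 0.332 SD |
| 0.6 | 0.64 | 0.80 | 1.56 | 0.256 SD | 0.306 SD |
| 0.7 | 0.51 | 0.71 | 1.96 | 0.229 SD | 0.273 SD |

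A plain change from baseline is no substitute. Its variance factor is 2(1 − r): 1.4 at r = 0.3, 1.0 at r = 0.5 and 0.6 at r = 0.7, so it is worse than ignoring the baseline when r is below 0.5.

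**Non-response.** A simulation assumed no true QoL effect and a logistic probability of missing the follow-up score that rises as baseline QoL falls (slope 0.5 or 1.0 per SD), with r of 0.3, 0.5 and 0.7. The false difference, intervention minus control, among available respondents was:

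| Missing, control / intervention (assumed) | Unadjusted difference | Baseline-adjusted difference |
|---|---|---|
| 30% / 30% | 0 | 0 |
| 25% / 15% | −0.014 to −0.057 SD | about 0 |
| 30% / 20% | −0.014 to −0.055 SD | about 0 |
| 40% / 20% | −0.028 to −0.111 SD | about 0 |

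For scale, the unadjusted standard error at 30% / 20% missing is √(1/107.1 + 1/122.4) = 0.132 SD, and at 40% / 20% it is √(1/91.8 + 1/122.4) = 0.138 SD. The false difference stays below one standard error in every setting, and it counts against the arm that keeps more of its sicker patients. Adjustment removes it here because missingness was made to depend on baseline QoL alone. Loss driven by later, unobserved decline would not be removed.

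**The case against.** The article is a condensed account, and the analysis plan is not shown. Covariates and repeated-measures models for a secondary scale are commonly left to that plan, and no sentence forbids using the baseline. QoL is declared descriptive, with no test, alpha or power claim. Unadjusted means in a randomized trial are valid, and choosing a median for a skewed bounded score is ordinary descriptive practice. The gain rests on an assumed correlation.

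Most of this limits the point without removing it. The article does more than stay silent: it names the summary measure, the presentation by survey date and the exclusion rule, and it makes adjustment conditional on serious bias, which does not address precision. That the baseline goes unused is an inference, but it follows from the method as written.

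A reader might infer more: that the plan drops incomplete patients altogether, compares selected survivors, and so gives a biased QoL result that a mixed model would repair. The documents do not support this. Exclusion is per sub-analysis, so someone without a month-12 score can still count at month 6. Missing-data mechanisms are to be examined. Mortality is itself a secondary outcome compared by arm. Selection biases the comparison only if loss differs by arm or acts on different patients in each arm, and no figure in the article shows that it will. Nor does a mixed model settle what QoL means after death; it treats those scores as merely missing.

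**Conclusion.** The point holds as one of efficiency and interpretability. The planned QoL comparison is valid but ignores a baseline score that the trial already collects. For an assumed correlation of 0.3 to 0.7, adjustment multiplies the variance by 0.91 to 0.51 and narrows confidence intervals by 5% to 29%, equivalent to 1.10 to 1.96 times the patients. It also reduces bias from differential non-response to the extent that baseline QoL explains that non-response. That bias is zero with equal, similarly driven loss, and was at most 0.11 SD in the settings tried.

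Truncation by death stays open under either analysis and needs a stated interpretation. QoL is secondary and descriptive, so no confirmatory error rate and no part of the primary analysis is affected.

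**What to change.** For each QoL scale, report the adjusted mean difference with 95% confidence interval at each visit, from ANCOVA or a mixed model for repeated measures. Include the baseline score and the stratification factors, center and age group (under 60, 60 or over). In the mixed model, let the arm effect and the baseline effect vary by visit. Use this in place of the mean/median switch; medians can stay as supporting description. Do not substitute an unadjusted change score.

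Beside each estimate, show by arm the number alive, the number of deaths and the number of completed questionnaires at that visit. State that the estimate refers to patients while alive, and that the model does not resolve truncation by death.

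State also when the baseline questionnaire is completed relative to disclosure of allocation. *Results* says patients were usually randomized several days before discharge, and the covariate should not be open to influence by the arm.

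The cost is analysis-plan wording and a standard model. No new data are needed, and first results are not expected until mid-2027, so the change can be made before analysis.
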